### Questionnaires

To gain insights into the satisfaction of guests about the worksite cafeterias, employees of all worksites will be asked to fill in an online questionnaire at baseline and after the intervention phase. The questionnaire assesses elements of the satisfaction with the worksite cafeteria and vitality with the Vita-16 [51]. Further, self-reported demographic variables will be collected like age, sex, body weight, height, level of education, marital status, household size, frequency of having lunch at the worksite cafeteria and the proportion of lunch purchased in the worksite cafeteria. Concepts like frequency of having lunch at the worksite cafeteria were tested by two researchers ([name]). They tested if the answer categories were appropriate and if questions were stated clear and neutrally. A small test panel of eight persons tested the questionnaire thereafter. They reviewed the questionnaire on clarity and gave feedback. The feedback was used to improve the questionnaire.

Also demographic characteristics of the companies will be measured by the researchers, like work sector (white collar, blue collar) and size of the company (amount of employees). Worksite cafeterias demographic and geographic characteristics that are measured are size (visitors daily), area (urban, suburban or rural), amount and proximity of competing lunch venues/purchase points for food, catering company (name, size and formula), contract form and mean amount of money spent per visitor per lunch.

### Statistical analysis sales data

We will use a linear mixed model (LMM) analysis to compare the intervention and control group. We distinguish three levels of data: time (level 1), the individual worksite cafeteria (level 2) and the catering companies (level 3). We adjust for this clustering of our data via a linear mixed model, including random intercepts and slopes where necessary according to the common procedure described in Twisk [52].

### Statistical analysis Worksite cafeteria Scan

The worksite cafeteria scan is an instrument to measure to which level the intervention is executed and if it is executed correctly. For each strategy can be filled out if this is executed (yes/no) and if it is correctly or incorrectly conducted. A percentage of correctly implemented strategies will be the result of the scan. Strategies that are not applicable will kept out the calculation.

We will not test for baseline differences based on arguments of De Boer et al. [53] to actively adopt the CONSORT 2010 statement by not publishing significance tests for baseline differences. Adjustment for prognostic variables will nevertheless be made. We will report results from the fully adjusted as well as crude analyses.

Also the level of correctly executing the intervention will be measured in the intervention group during the intervention phase (12 weeks, every 2 weeks) with longitudinal data analysis.

### Statistical analysis Questionnaire

By means of linear mixed model analyses differences between visitors of the intervention and control group worksite cafeterias will be obtained. Also differences in satisfaction with the worksite cafeteria before and during the intervention will be analyzed with a linear mixed model. Satisfaction with the worksite cafeteria will be subdivided in satisfaction with the products offered, the price of products and the way and order that products are placed. A regression analysis will be obtained to take possible confounding variables into account.

Descriptive statistics of the worksite cafeterias will be used to characterize the intervention and control group at baseline. Moreover, descriptive statistics will be used to identify satisfaction, food choice behavior and subjective health of all participating employees in the pre-test.

Statistical analyses will be conducted using standard statistical computer software (IBM SPSS Statistics 20.0) and MLwiN 2.35 software for mixed models. All statistical tests will be two-tailed and a 5% significance level will be maintained throughout the analyses.

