## Methods and research design

### Design

The effects of a healthier worksite cafeteria will be studied by means of a two-arm, (pre-stratified) randomized controlled trial (RCT). The RCT is designed to evaluate the effect of a 12-week intervention in the worksite cafeteria that is aimed at changing food choices in the worksite cafeteria towards healthier ones. A linear mixed model is used to also execute repeated measures. Primary outcomes are sales data of products in eight product groups, measured via cask register output. Secondary outcomes include satisfaction with the worksite cafeteria and vitality. The sample will include approximately 34 worksite cafeterias of 6 different catering companies. Worksite cafeterias will be randomly assigned (1:1) to the intervention or control arm. The randomization will be a block randomization with the size of worksite cafeterias (<500 or ≥500 customers daily) and order of inclusion as blocking variables, performed by the researcher. Outcome measures will be collected at baseline and weekly during the 12-week intervention phase to assess changes in food choice behavior of visitors. Figure 1 provides an overview of the timeline of the study design. The Medical Ethics Committee of the VU Medical Centre confirmed that this study does not apply to the Medical Research Involving Human Subject Act (WMO), due to the nature of the measurements (sales data and anonymous questionnaires).

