### Sample sizes

The power calculation is based on the main outcome measure of the linear mixed model: sales data of sandwiches, sandwich filling, salads, (hot) meals, fruit and vegetables, ‘combi-deals’, snacks and candy. Using a standard deviation of 10%, a sample of 15 intervention and 15 control worksite cafeterias are needed to detect a 20% mean increase in ‘better choice’ products between the intervention and the control group, at 80% power, a 5% level of significance and an estimated intra-cluster correlation (ICC) coefficient of sales within worksites of 0.15. The ICC represents how strongly sales in one worksite cafeteria are related. This increase of 20% is based on the sales of sandwiches and snacks in a pilot study testing this intervention (not published). The standard deviation of 10% is based on the same pilot study. To account for a possible 10% drop out of location or sudden difficulties like incorrect cash desk registration, 34 worksite restaurants will be randomized [26, 27, 29] and divided over the experimental group and the control group. By comparisons of the sales data between the experimental and the control group the effect of the healthy worksite cafeteria strategies can be studied.

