### Sales

Daily sales of sandwiches, sandwich filling, salads, (hot) meals, fruit and vegetables, ‘combi-deals’, snacks and candy will be registered for 15 weeks (3 weeks pre-measuring and 12 weeks intervention) in both intervention and control group worksite cafeterias.

All food products can be classified for relative healthiness, in one out of three categories within its product group. The classification is based on the levels of saturated fat and trans fat, added sugar, salt, dietary fiber and overall energy density [47–49]. Products can be classified in the following categories; the ‘preference category’, which is the most healthy category, the ‘middle category’ which is less healthy, but still reasonable, or the ‘exception category’, for products most unfavorable within the product category. The first two categories ‘preference category’ and ‘middle category’ are taken together into the so-called ‘better choice’. This provides a dichotomy within product groups; ‘better choice’ products, versus ‘exception’ products [48].

The primary outcome measure of this research project is the proportion of sales of ‘better choice’ products within the product categories sandwiches, sandwich filling, salads, (hot) meals and snacks and the sales of fruit and vegetables, ‘combi-deals’ and candy. The difference in (proportions of) sales of these products will be compared between the intervention group and the control group. All measured product categories correspond to the intervention strategies. In Dutch worksite cafeterias prepared sandwiches, bread combined with separate toppings or fillings and snacks are common lunch items [50], therefore certain intervention strategies target these products. The sales data will provide insight in the effect of the larger visible share, better pricing, placement and promotion of healthier ‘better choice’ products and the effects of not promoting less healthy products like snacks.

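### Eight product-group outcomes are all primary and each is tested at 5% with no rule for a positive trial, so the error rate across the primary outcomes is not held at 5%

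*Protocol article*

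**What the plan says.** Under Design, the article states: "Primary outcomes are sales data of products in eight product groups, measured via cask register output". The Sales section gives the composition: "The primary outcome measure of this research project is the proportion of sales of ‘better choice’ products within the product categories". Five groups are handled in this way, namely salads, snacks, hot meals, sandwiches and their fillings. The other three are measured as sales, as the end of the same sentence shows: "hot) meals and snacks and the sales of fruit and vegetables, ‘combi-deals’ and candy". The comparison follows: "The difference in (proportions of) sales of these products will be compared between the intervention group and the control group".

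The closing paragraph of Statistical analysis Questionnaire covers all analyses and sets the level: "All statistical tests will be two-tailed and a 5% significance level will be maintained throughout the analyses". The Sample sizes section also plans at an undivided 5%.

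Under Statistical analysis Worksite cafeteria Scan, the article says that adjustment for prognostic variables will be made, and adds: "We will report results from the fully adjusted as well as crude analyses". Neither version is named as the one that carries the conclusion.

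**The concern.** The research question is a single one: the effect of the healthier cafeteria on what employees buy. Eight primary tests bear on it, each at the full 5%, and nothing says how their results combine into an answer. A report could find one significant product group among eight and present it as a positive primary result while keeping to everything the article states. The article foresees wider roll-out through the caterers' trade association, so such a claim could have practical consequences.

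This is not a detail left to a statistical analysis plan. The article settles the level itself, for all tests, and a later plan with a multiplicity correction would depart from that sentence.

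**Working it through.** **Inputs from the article.** Eight primary outcomes (Design, Sales). Two-sided 5% for each test (Statistical analysis Questionnaire). SD 10%, difference 20%, 80% power, 5% level, ICC 0.15, 15 cafeterias per arm, 10% dropout, 34 randomized (Sample sizes). The article states no error rate across the eight outcomes and no correlation between them.

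**The plan's own figures.** The dropout step reproduces: 30 / 0.9 = 33.3, rounded up to 34. The 15 per arm does not follow from the stated difference and SD alone: 2 × (1.960 + 0.842)² × (10/20)² = 3.9, so 4 per arm (6 with a t-test). The ICC cannot be applied because no cluster size is given. That is a separate matter, but it means the cost of a correction has to be judged from the stated 80% power at 15 per arm, not from the ratio of 20 to 10.

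**Error rate over eight tests, all nulls true, any one significant result counted as success.**

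- Independent outcomes: 1 − 0.95⁸ = 1 − 0.663 = 0.337.
- Upper bound under any dependence: 8 × 0.05 = 0.40.
- Equal pairwise correlation r (assumed), eight two-sided normal tests, 1,000,000 simulated draws:

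| r | chance of at least one false positive |
|---|---|
| 0.1 | 33% |
| 0.3 | 30% |
| 0.5 | 25% |
| 0.7 | 19% |
| 0.9 | 12% |
| 1.0 | 5% |

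Among these equal-correlation cases, the rate returns to 5% only at perfect correlation.

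**Cost of a correction.** Holm's strictest step is 0.05 / 8 = 0.00625, with two-sided critical value 2.734. Suppose 15 per arm truly gives 80% power at 5%.

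- Normal approximation: Φ(1.960 + 0.842 − 2.734) = Φ(0.067) = 53%.
- t-test: 15 per arm with 80% power at 5% corresponds to a difference of 1.06 SD; at 0.00625 the power for that difference is 49%.
- Cafeterias per arm to restore 80% at that step: 15 × [(2.734 + 0.842) / (1.960 + 0.842)]² = 15 × 1.63 = 24.4, so about 25.

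These figures are for one outcome at the first step. Holm relaxes the level after each rejection (0.05/7, 0.05/6 and so on), so the loss is smaller when several groups respond.

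**The case against.** The strongest reply is that the article never says one significant group makes the trial positive. It asks what the effect is, and it ties each product group to particular intervention strategies, so the eight results can be read as eight separate answers. It is also plausible that the outcomes are strongly correlated, since one bundle of strategies acts on the same cafeterias and customers. Both points stand in part. The error rates above depend on the any-one-counts reading, and the true rate could lie near the lower end. But all eight are called primary, no other decision rule is given, and even at a correlation of 0.9 the rate is more than twice 5%.

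Three stronger readings are tempting but unsupported:

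- A reader might take the error rate to be 30% as a fact. That value needs a common correlation near 0.3, which the article does not give.
- A reader might count crude and adjusted results as two chances per outcome and arrive at a still higher rate. The article promises only to report both; it does not say that a win in either would count.
- A reader might infer that a correction is nearly free, because a difference of 20 with SD 10 is two standard deviations. That ignores the ICC and the article's own claim of 80% power at 15 per arm, under which the cost is substantial.

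**Conclusion.** The point holds. Eight co-primary outcomes, a uniform 5% level and no success rule leave the primary error rate uncontrolled. It is about 34% if the outcomes are independent and about 33% to 12% for assumed common correlations of 0.1 to 0.9. These figures rest on three assumptions: no true effect on any group, any single significant group being read as a positive primary result, and equal correlation between outcomes. The exact rate cannot be known from the article; that it exceeds the nominal 5% under that reading does not depend on a particular correlation short of perfect agreement. The missing choice between crude and adjusted results is a lesser part of the same gap.

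**What to change.** Either of two changes would do, fixed before the outcome data are analysed by arm.

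1. **Holm across the eight primary tests.** Use one pre-named analysis per outcome: the adjusted model, with the crude result as supportive. Claim an effect on a product group only if its Holm-adjusted p-value is below 0.05. Cost: about 50% power for one outcome at the strictest step, if 15 per arm truly gives 80% at 5%, and less loss when several groups respond. The Sample sizes section should then say that its power applies to a single unadjusted comparison.
2. **One named primary outcome, the others secondary.** This keeps the full 5% for the primary test. If the choice is a pooled better-choice share over the five groups where it is defined, fruit and vegetables, combi-deals and candy become secondary, because they are measured as sales rather than as shares.

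In either case, the sentence on the 5% level should be limited to match. The drafting takes a few sentences; the real costs are the power in option 1 and the demoted outcomes in option 2.

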## Discussion

The objective of this study was to develop an intervention (named: “the worksite cafeteria 2.0”) based on nudging and social marketing techniques to make purchase behavior of Dutch employees healthier. Furthermore, the aim was to describe the design of a study to measure the effect of multiple simultaneously executed strategies in “the worksite cafeteria 2.0” on purchasing behavior of visitors in Dutch worksite cafeterias. Thereby answering the research question: What is the effect of a healthier worksite cafeteria based on nudging and social marketing techniques on the purchasing behavior of employees?

To our knowledge there are no studies that made a combination of evidenced based strategies with nudging and social marketing strategies and that are tested in ‘real-life’. Whereby ‘real-life’ means in different real worksites with different catering companies.

We will discuss several strengths of this study. A first strength considering the design is the fact that the effect will be tested in real-life Dutch worksite cafeterias, taking the variety between catering companies and industrial branches into account. This has the advantage over other studies that it gives realistic insight in the effect of the intervention in real-life settings and increasing generalizability, but it also will provide insight in the support for such intervention. By means of organizing this intervention study one gets insight in the amount of effort it takes to convince several companies to implement the strategies, in other words, insight in the amount of support that is needed for continuous implementation.

Second, to choose worksite cafeterias as a target location gives the opportunity to reach many people at their daily routine of visiting the worksite cafeteria. Since people will not have to sign up themselves, probably also people who are not traditionally engaged in health promotion campaigns can be reached. This could be an addition to health interventions reaching mostly only motivated people. Offering a solution for those people not intrinsically motivated would fill a gap.

A third strength of this intervention development and trial is the collaboration with multiple stakeholders like several catering companies, the Netherlands Nutrition Centre, Ministry of Health, Youth on a Healthy Weight (JOGG) and Veneca. By means of involving several catering companies the intervention will be developed and tested in practice. Working with catering companies from the start can tackle the common gap between research and practice, especially in the practical feasibility. The collaboration with Veneca enables the implementation of “the worksite cafeteria 2.0” on a larger scale. The position of Veneca gives them the ability to reach all catering companies and other stakeholders needed when making agreements for contract catering industry.

The last strengths to mention concerning the design is that the effect will be tested with a randomized controlled trial and by using objective data collection, namely sales data. Randomly allocating worksite cafeterias to the intervention group or to the control group is considered the golden standard for determining the efficacy of interventions and objective data are preferred over subjective data.

Finally also the intervention itself has some important strengths. The use of nudging and social marketing strategies is a promising tactic in changing people’s behavior [54, 55]. Just changing the environment has the potential effect of not invoking negative reactions. Furthermore, executing effective strategies simultaneously can have a cumulative effect and could be more effective in a heterogeneous group.

The present study is also subject to some limitations that need to be acknowledged. First, when recruiting worksite cafeterias for the RCT some bias can be expected. Probably companies who are more interested in a healthy lifestyle are more willing to participate. These worksite cafeterias will probably already have a healthier assortment and therefore the effect could possibly be relatively small. Therefore, in recruiting worksites we will put extra effort in including companies with a so-called blue collar workforce. Second, although a minimum of strategies must be executed, some strategies will not be applicable in certain cafeterias which may result in diversity within the interventions tested. For example, offering a smaller portion of a hot meal is not applicable if a cafeteria does not sell hot meals. Non applicable strategies could lead to an intervention less effective and differences in the intervention could make it difficult to interpret the effect. However, also in the control group some strategies would have not be applicable in some worksites. This will reflect the real-life execution and effect of such intervention.

The third limitation is the possibility of missing or false data, as a result of incorrect registration of products at the cash desk. Although the majority of the worksite cafeterias scan most of their products at the cash desk, some products will be registered with buttons. This could lead to incorrect registration of products. A final limitation is that the correct realization of all strategies cannot be controlled by the research team every day. Catering employees will be trained to execute the strategies as correctly as possible and bi-weekly the research team will visit the intervention cafeterias unannounced to check whether the strategies are executed correctly.

In conclusion, this healthy worksite cafeteria intervention is based on a unique combination of nudging and social marketing techniques. It will facilitate employees to purchase healthier products in real-life worksite cafeterias. By developing this intervention with input of employees and in close cooperation with catering and nutrition experts and the most important catering companies in the Netherlands, it has a good chance of long-term implementation.
